#### Economic Evaluation

The economic evaluation will be performed from a societal and health care perspective. The time horizon of the economic evaluation is 6 months, thus discounting of costs and effects is not necessary. Both cost-effectiveness and cost-utility analyses will be performed. The cost-effectiveness analysis will be performed with the primary effect measure (ie, RNA). The cost-utility analysis will be performed with quality-adjusted life-years (QALYs). The patients’ EQ-5D-3L health states will be converted into utilities using the Dutch tariff, and QALYs will be calculated using linear interpolation between measurement points [43]. The analyses will be done according to the intention-to-treat principle. Missing cost and effect data will be imputed using multiple imputation after which results will be pooled using Rubin’s rules [44]. Cost and effect differences will be analyzed using multilevel analyses with a 2-level structure (ie, patient, hospital). The 95% CIs around the cost differences will be estimated using bias-corrected intervals with 5000 replications. The bootstrap replications will be stratified for hospital to account for the clustering of data [45]. Incremental cost-effectiveness ratios (ICERs) will be calculated by dividing the difference in mean total costs between the groups by the difference in mean effects. Uncertainty surrounding the ICERs will be graphically presented on cost-effectiveness planes. Cost-effectiveness acceptability curves will also be estimated illustrating the probability that the optimization and substitution of perioperative care by eHealth is cost effective in comparison with usual care for a range of different ceiling ratios. Various sensitivity analyses will be performed to assess the robustness of the results.

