##### Mobile Phone App (mHealth) and Activity Tracker

All information which is available on the website is also available on the mobile phone app (Ikherstel app), which will be synchronized with the website. This mHealth app has been developed because of the increasing use of mobile phone apps and in order to make the intervention more accessible. This means that the convalescence plan that is created by the patient on the website will also be displayed on the app. In addition, the app will offer some extra features, such as a section to make notes and the option to compose a list of what to pack when being admitted to hospital (Figure 7). If patients do not have a smartphone they will only use the website. Patients who have a smartphone may also receive an activity tracker (UP MOVE, Jawbone). Not all kinds of smartphones can be linked to this activity tracker, so only a proportion of the patients will receive an activity tracker. This activity tracker measures daily step count. We performed a pilot study with an accelerometer in 30 patients who underwent surgery that showed that the step count had a clear correlation with activity intensity levels (data not yet published, personal communication). Patients can link the activity tracker to the app. The activity tracker will be used as an aid for patients to monitor and to give feedback on their recovery. Patients are instructed to wear the accelerometer from the seventh day before surgery until 3 weeks after surgery and during the sixth week after surgery. In the week before surgery a baseline measurement will be performed. The mean step count per day of this week will be set as their target postoperative activity level. In the app, it will be displayed on which date this target level is expected to be reached (Figure 8). This date is based on the convalesce plan which is developed by the patient. After surgery, the daily step count will be graphically displayed in the app and on the website as a percentage of their target activity level. When no baseline measurement is performed (for example, because the period between inclusion and surgery is shorter than 1 week), the target activity level will be set at 7100 steps per day (based on the mean preoperative value of the pilot study). As the pilot study also indicated that the most improvement in activity level was detected in the first 2 weeks after surgery, it was decided to ask the patients to wear the accelerometer during the first 3 weeks after surgery. The sixth week was chosen because we hypothesize that baseline activity level will be reached in this week. Patients will be offered the opportunity to wear the activity tracker in the fourth and fifth week after surgery as well.

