	**Secondary outcome measures**									
		Participation (PROMIS short form Social Roles)		X		X	X	X		X
		Self-rated health (EuroQol-5D-3L)		X			X	X	X	X
		Return to work (Return to work questionnaire)				X	X	X	X	X
		Physical activity (IPAQ^c^)		X			X	X	X	
		Recovery (RI-5^d^)		X		X	X	X		
		Pain intensity (VAS^e^)				X	X	X		
		Patient satisfaction (Satisfaction questionnaire)							X	

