	**Cost measures**									
		Care program (Bottom-up approach)		X^f^						
		Health care utilization (Cost questionnaire)							X	X
		Informal care (Cost questionnaire)							X	X

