		**Productivity loss**								
			Presenteeism: iPCQ^g^ and WHO-HPQ^h^	X		X	X	X	X	X
			Absenteeism: iPCQ	X		X	X	X	X	X
			Unpaid productivity: Cost questionnaire						X	X

^a^T_0_: 1 month before surgery; T_1_: 1 week after surgery; T_2_: 3 weeks after surgery; T_3_: 6 weeks after surgery; T_4_: 3 months after surgery; T_5_: 6 months after surgery.

^b^PROMIS: Patient-Reported Outcomes Measurement Information System.

^c^IPAQ: International Physical Activity Questionnaire.

^d^RI-5: recovery specific quality of life questionnaire short form.

^e^VAS: visual analog scale.

^f^Measured by the research team.

^g^iPCQ: Institute for Medical Technology Assessment (iMTA) Productivity Cost Questionnaire.

^h^WHO-HPQ: World Health Organization—Health and Work Performance Questionnaire.

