##### Measurement and Valuation of Costs

Intervention costs will include all costs related to the development and implementation of the intervention and will be measured using a bottom-up microcosting approach (ie, detailed data will be collected regarding the quantity of resources consumed during the development and implementation of the intervention as well as their unit prices). All other cost categories will be measured using Web-based questionnaires administered at baseline and after 1 week, 3 weeks, 6 weeks, 3 months, and 6 months of follow-up (Table 2). Health care costs will include costs related to the use of primary care (eg, general practitioner), secondary care (eg, hospital visits), and medication. These costs will be valued using Dutch standard costs and, if unavailable, prices according to professional organizations [40]. Informal care will be valued using a recommended Dutch shadow price [40]. Absenteeism will be measured using the Institute for Medical Technology Assessment (iMTA) Productivity Cost Questionnaire (iPCQ) and valued in accordance with the friction cost approach using the estimated cost of productivity losses in the Netherlands [40,41]. Presenteeism costs will be measured using the iPCQ questionnaire and the World Health Organization Health and Work Performance Questionnaire and valued using the estimated cost of productivity losses in the Netherlands as well [42]. Unpaid productivity costs will be valued using the aforementioned recommended Dutch shadow price [40].

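### EQ-5D-3L is not scheduled at 1 week, so QALYs capture an early between-arm difference only as far as it persists at week 3; separately, the text and Table 2 disagree on when three cost categories are measured

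*Protocol article*

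**What the plan says.** **Utilities.** Under Economic Evaluation, EQ-5D-3L states are converted with the Dutch tariff and "QALYs will be calculated using linear interpolation between measurement points". In Table 2, the row beginning "Self-rated health (EuroQol-5D-3L" is marked at T0, T2, T3, T4 and T5; the T1 cell is empty. The footnote to Table 2 defines the times as "1 month before surgery; T_1_: 1 week after surgery; T_2_: 3 weeks after surgery; T_3_: 6 weeks after surgery", followed by 3 and 6 months. The Allocation and Data Collection sections place T0 anywhere in the month before surgery.

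**Course of recovery.** The section on the app and activity tracker reports from a pilot that "the most improvement in activity level was detected in the first 2 weeks after surgery". Of the sixth week it says "we hypothesize that baseline activity level will be reached in this week".

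**Costs.** Measurement and Valuation of Costs says that every category other than intervention costs is collected by web questionnaires "administered at baseline and after 1 week, 3 weeks, 6 weeks, 3 months, and 6 months of follow-up", and cites Table 2 for this. In Table 2, the row beginning "Health care utilization (Cost questionnaire" is marked at T4 and T5 only. So are informal care and unpaid productivity. Absenteeism and presenteeism are marked at all six times.

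**The concern.** The trial's hypothesis is faster recovery. The protocol's own pilot places the steepest gain in activity in the first 2 weeks, which lie wholly inside the one segment of the QALY curve that has no postoperative measurement at its start. If the arms differ in utility during those weeks, the planned calculation sees the difference only through its value at week 3. Incremental QALYs are the denominator of the cost-utility ratio, so a small absolute loss can be a sizeable share of it.

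The cost mismatch covers the same period. The care being substituted falls there: an outpatient visit usually at 4 to 8 weeks in the control arm, against a telephone call at 2 weeks plus eConsults. A reader cannot tell whether health care use in those weeks is collected as it occurs or only at 3 months, or whether these three categories have a baseline value.

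**Working it through.** **Is the empty T1 cell real?** Yes. In the same table, the rows for PROMIS physical functioning, participation, return to work, RI-5, pain, absenteeism and presenteeism carry a mark at T1. The gap is therefore not a shifted column, and a T1 questionnaire already goes out.

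**Figure to reproduce.** The protocol states no utility, QALY or cost figure. The sample size (285 events, 308 patients) does not enter this point.

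**Formula.** Let d1, d3 and d6 be the between-arm utility differences at weeks 1, 3 and 6. Assume no difference at surgery (T0 utility carried to that day), at 3 months (week 13) or at 6 months (week 26). Areas are in weeks, divided by 52 to give QALYs.

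- Weeks 0 to 3 with a week-1 point: 0.5·1·(0 + d1) + 0.5·2·(d1 + d3) = 1.5·d1 + d3
- Weeks 0 to 3 as planned: 0.5·3·(0 + d3) = 1.5·d3
- Missed: (1.5·d1 − 0.5·d3)/52 = 1.5·(d1 − d3/3)/52
- Weeks 3 to 6, identical in both: 1.5·(d3 + d6)
- Weeks 6 to 13, identical in both: 3.5·d6

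**Scenarios** (all differences are assumptions):

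| d1 / d3 / d6 | With week 1 | As planned | Missed | Share |
|---|---|---|---|---|
| 0.03 / 0.03 / 0.03 | 0.27/52 = 0.0052 | 0.24/52 = 0.0046 | 0.0006 | 11% |
| 0.05 / 0.03 / 0.01 | 0.20/52 = 0.0038 | 0.14/52 = 0.0027 | 0.0012 | 30% |
| 0.05 / 0 / 0 | 0.075/52 = 0.0014 | 0 | 0.0014 | 100% |
| 0.10 / 0 / 0 | 0.15/52 = 0.0029 | 0 | 0.0029 | 100% |

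The sign follows from the formula: the plan understates the gain whenever d1 exceeds one third of d3, as it would if the benefit is largest early.

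**Within one arm.** Assume utilities of 0.85 before surgery, 0.65 at week 1 and 0.85 at week 3. Leaving out week 1 overstates that patient's QALYs by 1.5·0.20/52 = 0.0058. If the dip is the same in both arms, the difference between arms is unaffected.

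**Cost schedule, side by side.**

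| Category | Text | Table 2 |
|---|---|---|
| Absenteeism | T0 to T5 | T0 to T5 |
| Presenteeism | T0 to T5 | T0 to T5 |
| Health care use | T0 to T5 | T4, T5 |
| Informal care | T0 to T5 | T4, T5 |
| Unpaid productivity | T0 to T5 | T4, T5 |

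Three of the five questionnaire-based categories lack the T0, T1, T2 and T3 collections that the text promises, and the text cites the table that it contradicts.

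**The case against.** The case against making much of this is fair in several respects.

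- The per-patient overstatement of 0.0058 QALY might be read as a bias in the result. It is not: it drops out when the dips are equal. Only a between-arm difference matters.
- A reader might infer that any early benefit is scored as zero. That needs arms that differ at week 1 and are equal at week 3. The protocol expects return to baseline activity in week 6 and describes guidance until full recovery, so some difference at weeks 3 and 6 is plausible, and EQ-5D-3L is measured at both.
- The pilot finding concerns activity in 30 patients. It is not evidence about utility, nor about when the arms separate.
- Early recovery is not ignored elsewhere: PROMIS physical functioning, participation, RI-5 and pain are collected at T1, and the cost-effectiveness analysis uses resumption dates as its effect measure.
- A reader might infer that the QALY model omits baseline utility. The article lists no covariates for that model, and silence in a condensed article does not show omission.
- A reader might infer that early costs are lost or rest on a 3-month recall. No recall period is given; the T4 questionnaire may cover all the time since surgery.

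All of this stands, and it limits the size of the point. It does not remove the missing T1 utility, its effect under the stated interpolation rule, or the contradiction between text and table.

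**Conclusion.** The point holds in a limited form. The planned QALYs give a between-arm difference before week 3 only the weight that its week-3 value carries. Under the assumed differences, the loss is about 0.0006 to 0.0029 QALY, or 11% to 100% of the gain depending on how fast it fades; the upper end needs the benefit to be gone by week 3. These figures rest on assumed utility differences and on carrying T0 to the day of surgery. If recovery is faster early with the intervention, the error is conservative for it. The utility gap is confined to the cost-utility analysis and leaves the primary outcome and sample size untouched.

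The cost contradiction needs no assumption. It concerns health care use, informal care and unpaid productivity only, and bears on the cost side of both economic analyses. The documents support a call to reconcile the passages, not a claim that early costs go unmeasured.

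**What to change.** 1. **Utility at T1.** Add EQ-5D-3L to the existing T1 questionnaire for patients not yet past that point, and use it in the QALY curve. This costs five short items, slight extra burden, and a measurement schedule that differs between earlier and later patients.
2. **Patients already past T1.** Report a sensitivity analysis over a stated range of week-1 utilities, allowing the arms to differ. The section already promises sensitivity analyses, so this costs only a specification. If collection can no longer change at all, state the limitation.
3. **Cost schedule.** Reconcile Measurement and Valuation of Costs with Table 2. Either administer the cost questionnaire at the time points in the text, which adds burden at four occasions, or correct the text and make the T4 recall period cover the whole time since surgery. The second route costs only wording if the questionnaire already asks this.
4. **Optional.** Adjust the QALY difference for baseline utility, which is already collected. This is a free improvement, not the correction of an error.

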## Results

The inclusion process started in September 2015. The expected end date is August 2016. The data collection process will last until February 2017 since the follow-up duration is 6 months. The results are expected in 2018. Data cleaning or analyses have not begun as of this article’s submission.

## Discussion

### Summary

In this RCT we will evaluate the effect of eHealth on RNA after abdominal surgery.

### Strengths and Limitations

In the earlier studies performed by our research group, the effect of the eHealth intervention was evaluated in terms of duration until RTW [16,46]. The reason the primary outcome measure in this study is changed to duration until RNA is that in the earlier studies only employed patients could participate; we believe that unemployed patients can also benefit from this eHealth care program to facilitate recovery. However, one of the reasons for chosing duration until RTW in the earlier performed studies was that this outcome measure was relatively easy to measure and objectify. Duration until RNA is more difficult to measure and objectify. Most studies using this outcome measure make use of fixed measurement instruments, which may contain questions not always applicable to all patients or may not represent the most relevant problems for patients. As far as we know, this is the first study in which RNA after surgery is measured by a measurement instrument tailored to the patient. A tailored instrument increases the validity and reliability of the primary outcome measure. The ultimate form of tailoring is computer-adaptive testing (CAT), in which after the first item, the selection of items is determined by the person’s responses to previous items. For example, Zanocco et al [47] used CAT to measure changes in patient-reported health before and after parathyroidectomy. PROMIS short forms and CATs are increasingly used as outcome measures across clinical studies in different fields [48]. In our study we will use individualized short forms because CAT software for use in the Netherlands is still under development [49]. Another strength of this study is that we developed a nonintervention (standard) website, which enables us to blind the patients to which group they are assigned. Blinding of the health care professionals, however, was not possible. But in our opinion this will not influence the study results, since the health care professionals do not play a substantial role in the intervention or of the data-collecting process. This study is also strengthened by the fact that state-of-the-art statistical methods, such as multiple imputation, bootstrapping, and multilevel analyses, will be used. A limitation of the study is the heterogeneity of surgical procedures. However, the Delphi study that we performed to compose the convalescence recommendations used in this study showed more or less the same convalescence recommendations for all surgical procedures, which suggests that the recovery periods of these surgical procedures are comparable [24,25]. In addition, the heterogeneity can be considered an advantage, because the results will be applicable to a broader population. Another limitation may be that the study is carried out in 7 hospitals, which means that the usual care that the control group receives can vary between hospitals. We tried to reduce this bias by stratifying the randomization by hospital. Finally, the baseline measurement with the activity tracker will be performed in the week before surgery and therefore cannot assure that the baseline measurement will give a representative view of the normal activity pattern of the patients. However, the patients who participate in the study will undergo elective surgery. This in general will mean that the patients will not be suffering from an acute illness or bedridden at the time of surgery. Although we cannot entirely rule out that the baseline measurement will be influenced, we nevertheless believe that the risk will be minimal.

### Comparison to Prior Work: What This Study Will Add

To our knowledge, there are 13 other studies which have evaluated an educational or supportive eHealth intervention in perioperative care [16,46,50-61]. Most of these studies were relatively small or did not perform a power calculation. Only 2 studies were carried out in patients undergoing abdominal surgery. In addition, almost all studies (12/13) aimed to evaluate the eHealth intervention in addition to usual care. Only 1 study aimed to evaluate eHealth as (partial) substitution of usual care; however, this study had no report of a power calculation and included patients undergoing orthopedic surgery. The most comparable study to ours is that of Bouwsma et al [46], which evaluated the cost-effectiveness of an eHealth intervention in patients undergoing gynecological surgery (results not yet published). The main differences with our study are the primary outcome measure (RNA vs RTW), the aim of the eHealth intervention (substitution of care vs additional care), and the patient population (working and nonworking men and women vs working women). A total of 9 studies found a significant positive effect of the eHealth intervention regarding an outcome measure focusing on the postoperative course. However, studies evaluating eHealth interventions in abdominal surgery to substitute usual care are lacking, which underlines the importance of this current study.

### Clinical Relevance

Improving the quality of perioperative care is required because postoperative care is limited due to the reduction in the length of hospital stay. In addition, because of the increasing demand for health care due to the aging population and personnel shortages in health care, it is necessary to deliver more efficient and cost effective perioperative care. This study will evaluate whether eHealth can be used to suit this purpose. It will both give insight for health care professionals by determining the best form of perioperative care and facilitate policy makers in deciding whether eHealth can be used to substitute usual care against lower costs. The generalizability of this study is high because the eHealth intervention will be evaluated in various types of surgical procedures and will only require minor adaptions in order to be applied to other types of procedures.

## Appendix

Multimedia Appendix 1 Further information on screenshots.

Multimedia Appendix 2 Selection of the Patient-Reported Outcomes Measurement Information System (PROMIS) physical functioning item bank version 1.2.

Multimedia Appendix 3 Peer review report 1.

Multimedia Appendix 4 Peer review report 2.

Multimedia Appendix 5 Peer review report 3.

## Abbreviations

CAT: computer-adaptive testing
eHealth: electronic health
EQ-5D-3L: EuroQol-5D (3 level)
HR: hazard ratio
ICER: incremental cost-effectiveness ratio
IPAQ: International Physical Activity Questionnaire
iPCQ: Institute for Medical Technology Assessment (iMTA) Productivity Cost Questionnaire
IRT: item response theory
mHealth: mobile health
PROMIS: Patient-Reported Outcomes Measurement Information System
QALY: quality-adjusted life-years
RCT: randomized controlled trial
RI-5: recovery specific quality of life questionnaire short form
RNA: return to normal activities
RTW: return to work
VAS: visual analog scale
WHO-HPQ: World Health Organization Health and Work Performance Questionnaire
